Due to insufficient patient-response-to treatments and various undesirable negative side effects, more and more scientific researchers in the medical area have begun to consider PPI step-down therapy in recent years. PPI step-down therapy means gradually reducing dosage and patients’ dependence on PPIs according to the outcome and symptoms changes of patients. Multiple strategies may be used to de-escalate (i.e., stop or reduce) PPIs, including abrupt PPI withdrawal, step down therapy, and H_2_ blocker (i.e., famotidine) substitution. However, one randomized controlled trial (RCT) study showed that about 68% patients experienced symptom recurrence after discontinuation of long-term PPI therapy [18], thus, meaning that stopping PPIs is not sufficient to control patients’ symptoms in a long-term period.

The use of complementary and alternative approaches has proven to have an effect on the treatment of NERD [19, 20]. In recent years, numerous studies have evaluated the clinical effectiveness of traditional Chinese Medicine (TCM) herbals for the treatment of NERD. A review article showed that in addition to their acid-suppressive properties, anti-inflammatory, and antioxidant activity of the herbal remedies, these herbal medicine seem to provide a safer and more effective treatment compared to their pharmaceutical drug counterparts. Herbal remedies used in human studies have led to the alleviation of heartburn and regurgitation related to NERD where PPI treatment has failed to show a promising effect. Moreover, herbal remedies appeared to have a longer-lasting therapeutic effect than conventional anti-secretory agents have [19]. A systematic review has reported that the total effective rate of TCM alone was superior to single PPIs or prokinetics for their clinical efficacy. TCM also has advantages in reducing recurrence rate and adverse events like constipation, faint headache experience, and nausea [21]. Although TCM has been examined for its ability to alleviate PPI-refractory symptoms, including the reduction of recurrence of these symptoms as well as improve the quality of life of patients, a high-level evidence-based support and thorough understanding of the underlying mechanisms of the action of TCM herbal remedies were lacking [22].

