#### Dropout criteria

Decision to exit the trial himself/herselfLoss to follow-upPoor complianceDiagnosis with other TCM syndromes or an order to withdraw by the TCM physicians

For the occurrence of patients presented with the above situation, we will consider making a suspension. In cases of dropout, the reason should be explained. If there are baseline pharmacodynamic data, the last main therapeutic effect index can be transferred to the final results for statistical analysis, and the CRF should be retained.

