#### Intervention group

Based on the curative effect of treating NERD in clinical practice, we selected three kinds of TCM granules based on TJ methodology. According to the different TCM syndromes, participants with stagnation of liver and stomach-heat syndrome will be treated with Tongjiang (TJ) granule, those with spleen deficiency and dampness-heat syndrome will be treated with Jianpiqinghua (JQ) granule, and those with intermingled heat and cold syndrome will be treated with Wenpiqingwei (WQ) granule. These herbal granules are available from the Xiyuan Hospital as an in-hospital preparation. TCM granules are concentrated herbal particles obtained by the mean of spray drying the hot water extract of a mixture of raw herbs. TCM granules are extracted with water to make an aqueous extract or decoction used for treatment. Each bag of granules (approximately 20 g) will be dissolved in 200 ml water and taken twice a day, 1 h after meal. Participants in all three groups cooperated with PPI step-down therapy. From week 1 to week 2 of treatment, the dose of PPIs will be half of the original dose, once a day, taken before bedtime. The PPIs will be replaced with famotidine 20 mg from week 3 to week 4, taken before bedtime. From week 5 to week 6, acid-suppressive drugs will be withdrawn, and only TCM granules will be administered. There will be 6 weeks of treatment and 4 weeks of follow-up.

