### Sample size estimation

According to the preliminary trial results from the team and to literature reports, the average effective rate of traditional Chinese medicine treatment for NERD is 90% [25]. The literature reports that the effective rate of PPIs in the treatment of NERD is between 50 and 90% [4, 26], so we used an average of 70%. The trial intends to conduct a superiority test of two independent sample proportions, using a margin of 0.02, an alpha risk of 0.05, and a beta risk of 0.20, assuming an attrition rate of approximately 20%. The estimated sample size is *N* = 174, including 87 cases in the intervention group and 87 cases in the placebo group.

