### Secondary outcomes

Secondary outcomes are the PPI withdrawal rate and symptoms recurrence rate, scales about minor symptoms, health-related quality of life, mental health, and TCM syndromes.PPI withdrawal rate and symptoms recurrence rate: During patient follow-up for the 4 weeks after the end of the treatment, according to the above scores, the number of recurrences and corresponding recurrence rates. The PPI withdrawal rate will calculated based on the number of people who no longer use PPIs at follow-up.Minor symptoms scale: Scoring the frequency and degree of clinical minor symptoms. For the frequency, 0 points indicates no symptoms, 1 points indicates < 1 day per week, 2 points indicates 1 day per week, 3 points indicates 2–3 days per week, 4 points indicates 4–5 days per week, and 5 points indicates 6–7 days per week. For the degree of symptoms, 1 points means no symptoms; 2 points means symptoms are mild; 3 points means symptoms are moderate, need to take medicine occasionally; 4 points means symptoms are severe, need to take medicine for long time; and 5 points means symptoms are very serious, and affecting daily life, need to take medicine for long time. Details are shown in Table 3.SF-36: As a concise health questionnaire, the SF-36 comprehensively evaluates the quality of life of the respondents from 8 dimensions including Physical Functioning (PF), Role-Physical (RP), Bodily Pain (BP), General Health (GH), Vitality (VT), Social Functioning (SF), Role-Emotiona (RE), and Mental Health (MH). It also contains another health dimension: Health Transition (HT), which is used to evaluate the overall change in health in the past year [30–33].PRO: This scale is for patients with FGIDs. It contains a total of 35 items, divided into 6 dimensions (regurgitation, dyspepsia, general condition, social function, defecation, psychology) to assess the influencing factors of chronic gastrointestinal diseases. Each item is graded on a 5-point scale, with a maximum of 4 points and a minimum of 0 points. The higher the score, the more severe the symptoms [34, 35].SAS: The SAS scale is a 20-item self-reported assessment device. Each question is scored on a Likert-type scale of 1 to 4 (based on the following replies: “a little of the time,” “some of the time,” “a good part of the time,” and “most of the time”). The total score is obtained by summing the assessment of the 20 items. The total score multiplied by 1.25 gives the standard score. A standard cutoff score of 50 is usually used to diagnose anxiety. The standard score ranges are 25–49 (normal range), 50–59 (mild anxiety), 60–69 (moderate anxiety), and 70 (severe anxiety) [36, 37].SDS: The Self-Rating Depression Scale (SDS) developed by Zung is a norm-referenced measure, used to screen adults for the potential presence of depressive disorders. The scale produces raw scores between 20 and 80; Zung recommended converting these to Index Scores (which ranged between 25 and 100) by the simple process of multiplying by 1.25. Zung’s recommended cut-off for identifying adults with depressive disorder was index scores of 50 and over [38]. We used in this study an index score of 53 (raw score 42); this was more appropriate for use with Chinese populations [39].GERD–HRQL: A total of 16 items are used to evaluate the symptoms of heartburn, regurgitation, and the effects of current medication on life. Each item is scored on a 6-point scale, from 0 to 5 points. A score of 0 indicates no symptoms, and a score of 5 indicates that symptoms are incapacitating when performing daily activities [40, 41].TCM syndromes scale: a 15-item scale based on *the Clinical Guideline of New Drugs for Traditional Chinese Medicine*. This scale evaluates the changes in TCM symptoms of the digestive tract and the whole body of the participants, including flatulence, stomachache, poor appetite, heartburn, belching, acid reflux, pharyngeal paraesthesia, thirst, distention in the lateral lower abdomen, fatigue, shortness of breath, unwillingness to speak, somatosensory heaviness, fear of cold, and loose stool. Each item is scored, with 1 being asymptomatic and 4 being severe. The higher the overall score, the more severe the overall symptoms [42].

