### Statistical analysis

This trial will use intention-to-treat (ITT) analysis as the main method to evaluate the outcome results. To deal with missing outcome variables that remain to be recorded, the last record data will be carried over to the end or a multiple imputation method will be used.

Statistical analysis will be conducted using the SPSS 21.0 software. The significance level is established at 0.05, and the limits of the confidence interval are 95%. Descriptive analysis and categorical variables will be described in frequency tables and as percentages or composition ratios; continuous variables will be described in terms of means and standard deviations (SDs), or medians, lower quartiles (P25), upper quartiles (P75), minimum values, and maximum values. Comparative analyses between two groups will be performed for categorical variables using the chi-squared test, Fisher’s exact probability method, the Wilcoxon rank-sum test, or the CMH test. Continuous variables that conform to a normal distribution will be compares using a *t*-test (for homogeneity of variance between groups, with 0.05 as the test level; if the variance is heterogeneous, the Welch-Satterthwaite *t*-test will be used), while those that conform to a non-normal distribution will be compared using the Wilcoxon rank-sum test or the Wilcoxon signed-rank test. Hypothesis testing will use the two-sided test uniformly, and *P* ≤ 0.05 will be considered statistically significant.

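### If last-record carry-forward is used for the follow-up endpoints, a participant with no record after week 6 is counted as off PPIs and, on a worsening definition, as not recurred

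*Protocol article*

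**What the plan says.** The Statistical analysis section sets the population and the missing-data rule together. On the population: "This trial will use intention-to-treat (ITT) analysis as the main method to evaluate the outcome results". On missing outcomes: "the last record data will be carried over to the end or a multiple imputation method will be used". It does not choose between the two methods and sets no endpoint apart. The Dropout criteria also use carry-forward: where baseline data exist, "the last main therapeutic effect index can be transferred to the final results for statistical analysis".

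Secondary outcomes places recurrence in the four weeks after treatment, judged from the symptom scores, without a threshold. For PPI use it says "The PPI withdrawal rate will calculated based on the number of people who no longer use PPIs at follow-up".

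The step-down is set out under Intervention group and applies equally to the control group:

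- Weeks 1–2: "From week 1 to week 2 of treatment, the dose of PPIs will be half of the original dose".
- Weeks 3–4: "The PPIs will be replaced with famotidine 20 mg from week 3 to week 4".
- Weeks 5–6: no acid suppression; granules (or placebo) only.

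Table 1 schedules the VAS and the symptom scales at weeks 8 and 10. As printed, it marks cointerventions only for weeks 1 to 6.

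**The concern.** Carry-forward assumes that the last observed value is a fair stand-in for the missing one. For these two endpoints it is not. The last value before follow-up was taken before the outcome window opened, and for PPI use it was fixed by the treatment schedule. It says nothing about what the participant did once the trial regimen ended. People who relapse and go back to their own medication may also be the ones least inclined to return, so the loss may be related to the outcome.

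The endpoints are secondary, but the article's Discussion rests its expected benefits on them: less recurrence and less dependence on PPIs. A missing-data method that tends to supply the favourable answer for absent participants weakens the evidence for both.

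**Working it through.** **The plan's own figures.** The article gives no expected rate for recurrence or PPI withdrawal in this trial, so there is no planned value to reproduce for either. Its one derived figure, 174, can be reproduced: 0.30 × (1.960 + 0.842)² / 0.18² = 72.67 per arm, and 72.67 × 1.20 = 87.2, that is 87 per arm. The present point leaves that figure unchanged.

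**Inputs.**

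- d = share of an arm that completes week 6 but has no week 8 or week 10 record. The article does not give it. Sample size estimation says "assuming an attrition rate of approximately 20" per cent, without timing. I take d = 5%, 10% and 20%; the last puts all planned attrition after week 6 and is an upper bound.
- r = true recurrence. The Background reports from a cited trial that "about 68% patients experienced symptom recurrence after discontinuation of long-term PPI therapy". I use 68% as the high scenario, with 50% and 30% as assumed lower ones. Applying 68% to a four-week window is itself an assumption.
- q = true share off PPIs at follow-up, set to 1 − r for illustration only.
- The lost and the retained are assumed to have the same true rates.
- Recurrence is assumed to mean worsening after week 6.

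**Recurrence when week 6 is the last record.** The carried value shows zero change since the end of treatment, so none of these participants counts as recurred. Reported rate = (1 − d) × r; understatement = d × r.

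| d | r = 30% | r = 50% | r = 68% |
|---|---|---|---|
| 5% | 28.5% (−1.5) | 47.5% (−2.5) | 64.6% (−3.4) |
| 10% | 27.0% (−3.0) | 45.0% (−5.0) | 61.2% (−6.8) |
| 20% | 24.0% (−6.0) | 40.0% (−10.0) | 54.4% (−13.6) |

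**Some leave after week 8 instead.** Suppose half of the lost have a week 8 record and half of recurrences are visible by then. With d = 20% and r = 68%, the reported rate is 0.80 × 0.68 + 0.20 × 0.5 × 0.5 × 0.68 = 0.544 + 0.034 = 57.8%. The bias is smaller but remains.

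**PPI withdrawal when week 6 is the last record.** Reported rate = (1 − d) × q + d; overstatement = d × (1 − q). At d = 20%, true rates of 70%, 50% and 32% become 76%, 60% and 45.6%.

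**PPI withdrawal over all dropouts.** Leavers in weeks 1–2 are carried forward as on PPI. If all 20% leave then, 50% becomes 0.80 × 0.50 = 40%. If losses split equally over weeks 1–2, weeks 3–6 and after week 6, two thirds are carried as off PPI:

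- true 50%: 0.80 × 0.50 + 0.20 × 2/3 = 53.3%
- true 70%: 0.80 × 0.70 + 0.20 × 2/3 = 69.3%

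The sign changes with the timing of loss and with the true rate.

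**Between-arm difference (assumed losses after week 6).**

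- True 68% in both arms, loss 15% against 5%: 0.85 × 0.68 = 57.8% against 0.95 × 0.68 = 64.6%, an apparent gap of 6.8 points where none exists.
- True 48% against 68%, loss 10% against 20%: 0.90 × 0.48 = 43.2% against 0.80 × 0.68 = 54.4%, so a 20-point difference is reported as 11.2.

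The first example creates a difference and the second shrinks one.

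**The case against.** The strongest reply is that the plan does not commit to carry-forward. Multiple imputation is equally permitted and does not force this result. The choice by endpoint may also sit in an analysis plan or full protocol that is not shown. This stands as far as it goes: the point is conditional. It is not a complaint about missing detail, however. The article names carry-forward as acceptable for missing outcomes generally, and for these two endpoints it is unsuitable.

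A second reply is that follow-up PPI use is first observed at follow-up, so an absent participant might simply not be counted among those withdrawn. The text permits that reading, and it would bias the rate the other way. Nothing in the article decides between the two, which is a further reason to state the rule.

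A reader might infer more than the documents support:

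- *That everyone lost after week 6 is scored favourably.* Someone who leaves after week 8 carries a week 8 symptom record, which may already show recurrence.
- *That PPI withdrawal is necessarily overstated.* Early leavers on half-dose PPI pull the other way.
- *That a carried week 6 value can never count as a recurrence.* If recurrence were a score above a cut-off, a participant still symptomatic at week 6 could be carried forward as recurred.
- *That the comparison is biased towards the granules.* The article gives no loss by arm and no basis for predicting it.

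**Conclusion.** The point holds in conditional form. Under the carry-forward option, a participant who completes week 6 and has no later record is counted as off PPIs because of the schedule and, if recurrence means worsening after week 6, as not recurred. The understatement of recurrence in each arm is then about 1.5 to 13.6 points for assumed losses of 5–20% and recurrence of 30–68%. The top of that range is an upper bound on loss combined with a background figure that was not a planning assumption. It would be larger if those who relapse are more likely to be lost, and smaller if some of the lost have a week 8 record.

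For PPI withdrawal the overstatement is established only for these same participants; the direction over all dropouts is open. The effect on the difference between arms cannot be signed from the article. This is a worthwhile and inexpensive correction to two secondary outcomes. It does not bear on the primary VAS, on participants terminated in weeks 5–6, or on the sample size of 174.

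**What to change.** In Statistical analysis:

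1. State that for recurrence and PPI withdrawal no value from week 6 or earlier is carried forward.
2. Name multiple imputation, done by arm, as the main method for missing week 8 and week 10 data on these two endpoints. The plan already permits it.
3. Add a sensitivity analysis that counts participants with missing follow-up as recurred and as on PPI.

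The cost is a few lines of text, slightly more analysis work, and somewhat less favourable reported rates than carry-forward from week 6 would give. No change to recruitment or treatment is needed.

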### Primary outcomes

The primary outcomes are the VAS for heartburn and regurgitation and the major symptoms scale.The VAS is a line marked with 10 scales, with 0 points to 10 points at both ends. Zero points indicates no symptoms, and 10 points represents the most severe and unbearable symptoms. 0–2 is classified as “basic no symptoms,” 3–5 is classified as “mild,” 6–8 is classified as “moderate,” and 8–10 is classified as “severe” [27–29]. Patients will be given a VAS for regurgitation and heartburn daily through a diary card, and the average score of the two symptoms each week will be evaluated according to the content of the diary card. Participants were defined as responders if for at least 50% of weeks during the 6 weeks of the trial the weekly VAS score was reduced from baseline by ≥ 50%. We will calculate the percentage of responders. At the same time, the change in VAS score will be compared between groups.Major symptoms scale: For the main clinical symptoms of NERD, heartburn frequency, heartburn relief time, and regurgitation frequency, the scoring criteria are shown in Table 2.

**Table 2 Tab2:** Major symptoms scale

	Score		
	Mild (0)	Moderate (1)	Severe (2)
Symptom			
Heartburn frequency	1 day a week	2–3 days a week	4–7 days a week
Heartburn relief time	Relieve within 1h	Relieve within 1-3h	> 3 h does not relieve even all day
Regurgitation frequency	1 day a week	2–3 days a week	4–7 days a week

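### The test for VAS change is chosen by the data and uses baseline and centre poorly; one baseline-adjusted analysis should be named in advance

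*Protocol article*

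**What the plan says.** Under Primary outcomes, the VAS for heartburn and regurgitation is primary and is used in two ways. One is a binary responder summary ("We will calculate the percentage of responders"). The other is continuous: "the change in VAS score will be compared between groups".

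The Statistical analysis section gives one generic rule for every continuous variable:

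- Normal data: "Continuous variables that conform to a normal distribution will be compares using a" t-test, with a check "for homogeneity of variance between groups, with 0.05 as the test level".
- Normal data, unequal variances: "if the variance is heterogeneous, the Welch-Satterthwaite" t-test.
- Non-normal data: they "will be compared using the Wilcoxon rank-sum test or the Wilcoxon signed-rank test".

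No normality test is named, and nothing says when signed-rank rather than rank-sum applies. On level and sidedness: "The significance level is established at 0.05" and "Hypothesis testing will use the two-sided test uniformly". No method listed for continuous outcomes includes a baseline covariate or centre. Yet Table 1 schedules the VAS at week 0 and weekly from week 1 to week 6, and the Randomization and blinding section stratifies by centre.

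**The concern.** A t-test addresses a difference in means. A rank-sum test addresses whether values in one arm tend to exceed those in the other. If a preliminary look at the trial's own data decides between them, the meaning of a primary comparison is not fixed beforehand.

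Three further weaknesses follow from the wording:

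- The variance check protects only the normal branch. On the non-normal branch there is no safeguard for unequal spread, which is where rank-sum and a mean comparison part company.
- Signed-rank is a paired test. Two independent arms have no natural pairs, so without a stated within-arm purpose the wording leaves room for misuse.
- A simple change score with no centre term gives up precision that data already being collected could supply.

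**Working it through.** **1. The plan's own figure, and whether it is touched.** The Sample size estimation section uses rates of 90% and 70%, margin 0.02, alpha 0.05, power 80% and 20% attrition. With two-sided alpha and unpooled variance:

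n = (1.960 + 0.842)² × (0.9×0.1 + 0.7×0.3) / (0.20 − 0.02)² = 72.67 per arm; × 1.2 = 87.2.

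This reproduces 87 per arm, 174 in total. The figure rests on a proportion, so the choice of test for VAS change does not alter it. With 20% attrition about 70 per arm remain (87 × 0.8 = 69.6), so 70 and 87 per arm are used below.

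**2. Does the data-driven rule change the test?** Assumptions, because the article names no pre-test: Shapiro-Wilk in each arm at 0.05, then Levene at 0.05, then pooled t, Welch or rank-sum. For a bounded VAS-like change (assumed baseline mean 6, SD 1.5, scores held within 0-10) with identical arms of 87, the same population went to the pooled t-test in 81% of simulated trials, Welch in 4% and rank-sum in 14%. Sampling chance alone moved the hypothesis being tested.

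**3. Error rate with no mean difference** (4,000 to 6,000 simulated trials per scenario; Monte Carlo SE about 0.003 at 6,000):

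| Scenario | Stated rule | Welch always |
|---|---|---|
| Same distribution in both arms (normal, gamma, exponential, bounded VAS change) | 4.3-5.1% | 4.3-5.3% |
| Normal, SD ratio 1.5 | 4.9-5.2% | 4.7-5.0% |
| Gamma (shape 2), SD ratio 1.25 | 8-9% | about 5% |
| Gamma (shape 2), SD ratio 1.5 | 14-17% | about 5% |
| Gamma (shape 2), SD ratio 2 | 26-31% | about 5% |

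With stronger (exponential) skew and SD ratio 1.5, the rule gave 30.7% at 70 per arm and 37.0% at 87. The excess grows with sample size because rank-sum is then detecting a real difference in shape, not a difference in means.

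**4. Signed-rank on arbitrarily paired arms** (normal data, 70 per arm): size 4.9%; power 77.5%, against 77.7% for rank-sum and 80.3% for the t-test. Its level is not inflated. The fault is arbitrariness: at about 80% power, re-pairing the same data at random reversed significance in 7% of simulated trials.

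**5. Baseline adjustment.** Let the baseline and follow-up variances both be σ² with correlation ρ.

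- Change score: 2σ²(1 − ρ).
- ANCOVA: σ²(1 − ρ²).
- Ratio: (1 − ρ²) / [2(1 − ρ)] = (1 + ρ)/2.

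| Assumed ρ | ANCOVA variance / change variance | Extra participants the change score needs (1/ratio − 1) | ANCOVA power where change score has 80% at 70 per arm |
|---|---|---|---|
| 0.3 | 0.65 | 54% | 93.5% |
| 0.5 | 0.75 | 33% | 89.9% |
| 0.7 | 0.85 | 18% | 86.0% |

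If the variances differ, with k = baseline SD / follow-up SD, the change-score variance exceeds the ANCOVA variance by σ_f²(k − ρ)², where σ_f is the follow-up SD. This is never negative, so the direction holds although the ratio moves. A mean over several weeks would usually have its own k and ρ. The gain from centre cannot be sized, because the article gives no between-centre variation.

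**The case against.** The strongest reply has five parts.

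**A reader might infer that the rule breaks the 5% level in general.** The documents do not support that. If treatment does nothing, randomised arms share one distribution and the rule holds its level. The high figures need equal means, skewness and unequal spread together, and the article gives no VAS SD, skew or ratio. This stands, and limits the error-rate point to a conditional one.

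**A reader might infer that a paired test is prescribed between arms.** The phrase about comparing two groups opens the sentence on categorical variables; the continuous sentence is separate and may intend signed-rank for baseline-to-follow-up change. This stands: it is an ambiguity, not a stated invalid test.

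**A reader might infer that baseline is ignored.** A change score subtracts baseline, and the responder definition is relative to baseline. This stands: baseline is used, but inefficiently.

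**The article nowhere says that mean change is the target, and ranks can win.** In a simulated gamma-skewed shift the rule had 92% power against 80% for Welch. This is fair, and it is why rank-sum merits a place as a sensitivity analysis. It does not excuse leaving the target to be settled by the data.

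**Covariates and models are commonly left to an analysis plan that is not shown.** Silence would not be a finding. Here the article is not silent: it fixes a specific rule that governs a primary comparison.

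**Conclusion.** The point holds in a limited form. The article fixes a data-dependent choice of test for a primary comparison, so the quantity tested may be a mean difference or a rank contrast. It also lists a paired test without stating its purpose, and its continuous analyses use neither a baseline covariate nor the stratification factor.

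Loss of error control for a difference in mean change is a risk only where skewness and unequal spread coincide: about 8-9%, 14-17% and 26-31% at SD ratios of 1.25, 1.5 and 2. Those figures rest on assumed gamma data and assumed pre-tests, and should not be read as the trial's actual error rate.

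The firmer gain is precision. ANCOVA needs 15% to 35% less variance than the change score at ρ from 0.7 to 0.3, assuming equal variances and correlations that the article does not give. The change should be made, but the trial's validity does not hang on it.

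**What to change.** Remove the normality and variance pre-tests, and name one primary analysis of VAS change in advance. One workable form is ANCOVA of each patient's mean weekly VAS over weeks 1 to 6, with baseline VAS and centre as covariates and heteroscedasticity-robust standard errors. One pre-stated week, or a repeated-measures model, would also serve. The text must say which, because six weekly on-treatment scores exist and a reference to weekly VAS alone would leave the choice open.

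Then state that:

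- Welch's t-test is used wherever a mean comparison is unadjusted;
- rank-sum is a sensitivity analysis;
- signed-rank is for within-arm change only.

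The cost is statistical wording, settled before unblinding. The week-0 and weekly VAS are already scheduled, centre is already recorded as a stratification factor, and 174 participants remain the target.
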